### 2.4. Data management

To ensure the confidentiality of information, every participant will be assigned with a unique identifier linking to personal data, which is accessible by a trained research assistant. The completeness and plausibility of data from all assessments will be ensured by the responsible investigators for quality control. All study investigators will comply with the sponsor audit requirements. During all stages of the study, auditing can be carried out by independent individuals appointed by the sponsor to ensure the quality of the study and the validity of the results.

### 2.5. Statistical considerations

#### 1.2.5. Sample size.

This is a pilot study that examines the possible relationship of PCSK9 expression and its association with platelet reactivity and platelet-ox-LDL binding. A sample size between 24 and 50 participants has been recommended for a pilot study.^[25]^ In addition, the appropriate sample size of a pilot study should be calculated in relation to other similar studies.^[26]^ According to previous research,^[27]^ with the consideration of estimated attrition rate of 20%, a total of 115 patients will be recruited in the present study.

#### 2.2.5. Statistical analysis.

Categorical variables will be reported as counts (percentage). Distribution of continuous variables will be assessed by the Kolmogorov-Smirnov test. Normally-distributed continuous variables will be expressed as mean ± SD. Non-normally distributed continuous variables will be expressed as median and interquartile range (IQR). Comparisons between the groups will be performed by Pearson chi-squared test, analysis of variance or Kruskal-Wallis test, as appropriate. The association of PCSK9 levels with platelet reactivity and ox-LDL-platelet binding will be evaluated by Spearman rank test. For further analysis, we will divide the cohort into tertiles of PCSK9 values. univariate and multivariate logistic regression will be used to analyze the association between PCSK9 levels with on-treatment platelet reactivity. All tests will be 2-sided with an alpha level of 0.05. Analysis will be performed using SPSS version 20.0 (SPSS Inc., Chicago, Illinois).

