## Abstract

**Method and design::**

In this pilot cross-sectional study, we will enroll 115 Chinese participants aged 30 to 75 years with ACS. Blood sample will be obtained after the first maintenance dose of aspirin and clopidogrel during morning time. Serum PCSK9 will be measured by an enzyme-linked immunoadsorbent assay. Platelet reactivity will be assessed by; Platelet activation (P-selectin and GPIIbIIIa expression using flow cytometry) and; Platelet aggregation using light transmission aggregometry in response to various stimuli. On-treatment platelet reactivity is measured by adenosine diphosphate-induced platelet aggregation. Binding of ox-LDL to platelet will be evaluated by flow cytometry. Spearman correlations will be used to determine association of serum PCSK9 with platelet functional parameters and platelet-ox-LDL binding. Additionally, continuous PCSK9 levels will be categorized into tertiles of equal size to investigate its association with on-treatment platelet reactivity.

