#### 3.2.3. Platelet aggregation assay.

Platelet aggregation will be analyzed using light transmission aggregometry according to standard protocols.^[21,22,23]^ Sodium citrate anticoagulated whole blood will be handled within 1 hour. Samples will be centrifugated at 260g for 10 minutes to obtain platelet rich plasma (PRP) and additionally at 760g for 10 minutes to obtain platelet-poor plasma. Platelet concentration in PRP will be adjusted to 2 × 10^8^/mL by dilution with homologous platelet-poor plasma. After stimulation of ADP (10µmol/L) or (arachidonic acid, 0.5 mmol/L), adjusted PRP will be utilized for the assay and light transmission will be monitored by an aggregometer over 6 minutes. Aggregation is quantified with 100% aggregation corresponding to 100% light transmission and maximum platelet aggregation rate (MPAR) will be used for statistical analysis. ADP- and arachidonic acid -induced platelet aggregation will be recorded as MPAR_ADP_ and MPAR_AA_, respectively. In addition, we define high on treatment platelet reactivity (HTPR) as MPAR_ADP_ >59%.^[24]^

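### The only adjusted analysis named is a logistic model that appears to cut MPAR_ADP at 59% and PCSK9 into tertiles, which would lose about half the information; a regression on the continuous values should lead

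*Protocol article*

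**What the plan says.** The relevant statements are spread over four places in the protocol article.

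- **Statistical analysis (2.2.5).** Associations of PCSK9 with platelet reactivity and ox-LDL binding are tested by Spearman rank correlation, without adjustment. Then: "For further analysis, we will divide the cohort into tertiles of PCSK9 values". The next sentence reads: "univariate and multivariate logistic regression will be used to analyze the association between PCSK9 levels with on-treatment platelet reactivity". This is the only multivariable method named. Also: "All tests will be 2-sided with an alpha level of 0.05".
- **Abstract, Method and design.** "continuous PCSK9 levels will be categorized into tertiles of equal size to investigate its association with on-treatment platelet reactivity". No model is named there.
- **Platelet aggregation assay (3.2.3).** Maximum aggregation is recorded as a percentage, and "we define high on treatment platelet reactivity (HTPR) as MPAR_ADP_ >59" per cent. No other binary reactivity outcome is defined.
- **Sample size (1.2.5).** "with the consideration of estimated attrition rate of 20%, a total of 115 patients will be recruited". The article gives no effect size, target power, HTPR prevalence or number of covariates.

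**The concern.** Logistic regression needs a categorical outcome, and HTPR is the only one on offer. Read with the abstract, the tertiles appear to be the exposure. If so, two continuous measurements are both cut before the one analysis that can address confounding. In an observational study that analysis carries much of the weight, and the Discussion itself stresses limiting confounding of platelet reactivity.

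At stake is the precision of the adjusted estimate. A weak adjusted odds ratio beside a clear Spearman correlation would be harder to interpret, because lost information and removed confounding can both produce that pattern. Tertile cut-points also depend on the sample and do not carry over to another study.

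**Working it through.** **Inputs from the article.** 115 recruited, 20% attrition, two-sided alpha 0.05, HTPR cut at 59%, PCSK9 in tertiles.

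**Assumptions.** Correlation between PCSK9 and MPAR_ADP 0.20 to 0.40; HTPR prevalence p of 20% to 50%; bivariate normal data; no covariates.

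**1. The article's own figure.** 115 cannot be derived forwards, since its base number, effect size and power are not stated. Backwards, 92 / (1 − 0.20) = 115, so 115 × 0.8 = 92 evaluable patients, or about 31 per tertile.

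**2. Information retained.** For small effects:

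- Cutting the outcome keeps φ(z)² / [p(1 − p)], with z the normal cut-point. At p = 0.20: 0.280² / 0.16 = 0.49. At p = 0.50: 0.399² / 0.25 = 0.64.
- Cutting the exposure into equal tertiles keeps 6φ(z)² at the two-thirds point: 6 × 0.3636² = 0.79.
- Both cuts keep the product.

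| HTPR prevalence | Outcome cut only | Both cuts |
|---|---|---|
| 20% | 0.490 | 0.389 |
| 30% | 0.576 | 0.457 |
| 40% | 0.622 | 0.493 |
| 50% | 0.637 | 0.505 |

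The loss is therefore about 49% to 61% with both cuts, and about 36% to 51% if PCSK9 enters as continuous. With both cuts, 92 patients are worth about 92 × 0.389 = 36 to 92 × 0.505 = 46 patients analysed on the continuous scale.

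**3. Power at n = 92.** For the continuous test, Fisher's z gives Φ(atanh(r)·√(n − 3) − 1.96). At r = 0.30: 0.3095 × 9.434 − 1.96 = 0.96, so power is 0.83. The logistic models were simulated with 3,000 data sets per setting and likelihood-ratio tests. Ranges run over prevalence 20% to 50%.

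| Assumed r | Linear, both continuous | Logistic, PCSK9 continuous | Logistic, tertile trend (1 df) | Logistic, tertiles (2 df) |
|---|---|---|---|---|
| 0.20 | 0.48 | 0.29–0.35 | 0.24–0.27 | 0.19–0.24 |
| 0.30 | 0.83 | 0.53–0.65 | 0.43–0.52 | 0.35–0.46 |
| 0.40 | 0.98 | 0.80–0.89 | 0.71–0.79 | 0.60–0.74 |

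Without any attrition (n = 115, r = 0.30), the linear test has about 0.91 and the 2-df tertile test 0.42 to 0.55.

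**4. Events.** 92 × 0.20, 0.30, 0.40 and 0.50 gives about 18, 28, 37 and 46 events. At 10 events per parameter this supports 1.8, 2.8, 3.7 and 4.6 parameters, two of which the tertiles use. At 5 per parameter it supports 3.7 to 9.2. With all 115 patients the range at 10 per parameter is 2.3 to 5.8. Above 50% prevalence the non-events become the limit.

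**The case against.** The strongest reply is that the coding is inferred. The logistic sentence speaks only of PCSK9 levels, the tertile sentence stands apart, and the tertiles might serve the group comparisons by analysis of variance or Kruskal-Wallis that the same section plans. This stands: the tertile exposure is the natural reading, not a stated fact. It does not remove the point, because the outcome must still be binary, and that cut alone loses 36% to 51% of the information.

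Four stronger readings are tempting, and the article does not support them.

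- **Nearly half the power is always lost.** The relative loss depends on the unknown correlation and on the test. Across correlations of 0.20 to 0.40 it runs from about 19% to 62% and is near half only at about 0.20 to 0.30. The stable statement concerns information, not power.
- **There are too few events for the model.** Prevalence and covariate count are not given, and a condensed article may leave the covariate list to the full protocol or analysis plan. At 40% to 50% prevalence with few covariates the model is feasible, and 10 events per parameter is a rule of thumb.
- **A null adjusted odds ratio would be uninterpretable.** Univariate logistic regression is also planned. Crude and adjusted odds ratios under the same coding help to separate confounding from lost information.
- **The continuous data are thrown away.** Spearman uses them, though without adjustment.

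Two further caveats stand. The simulation has no covariates, so it compares codings and does not give the power of the adjusted model. Bivariate normality also favours the linear model, whereas MPAR_ADP is a bounded percentage. The pilot label and the acknowledged small sample lower the stakes, but they also make it harder to afford the loss. HTPR is a cited threshold that answers a question of its own, which is a reason to keep it as support.

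**Conclusion.** The point holds in a conditional form. Logistic regression is the only adjusted analysis named; it needs a binary outcome, and HTPR is the only one defined. If tertiles are the exposure, as the text suggests, about 49% to 61% of the information is lost; if PCSK9 stays continuous, about 36% to 51%. At 92 patients and an assumed correlation of 0.30, unadjusted power is 0.35 to 0.46 (2-df tertile test) or 0.53 to 0.65 (continuous PCSK9), against 0.83 for the continuous linear test. The adjusted model may carry only about 2 to 4 parameters at 10 events each.

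These figures rest on bivariate normality, the assumed correlation and the assumed prevalence. The article does not show that the model must fail or that its result could not be interpreted. It does show that a more precise adjusted analysis is available from measurements already planned. The change should be made, but the study does not depend on it.

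**What to change.** 1. Make the main adjusted analysis a linear regression of continuous MPAR_ADP on continuous, log-transformed PCSK9, with the same covariates planned for the logistic model. Use robust standard errors, or a rank-based regression if MPAR_ADP is clearly non-normal, and report the slope with a 95% confidence interval.
2. Keep the HTPR logistic model as supportive, with PCSK9 continuous and few covariates, or Firth-penalised.
3. Use PCSK9 tertiles for description.
4. State outright the outcome and the exposure coding of each model.

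The cost is a change of wording; no further patients, samples or assays are needed. The downside is that the headline becomes a slope in percentage points of aggregation rather than an odds ratio, which the supportive HTPR model still supplies.

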## 3. Discussion

Patients who had a recent ACS remain at high risk of recurrent ischemic events despite the current evidence-based treatments, including dual antiplatelet therapy and lipid-lowering agents.^[28]^ Circulating levels of PCSK9 dynamically increase during ACS as a consequence of cardiac ischemia.^[29]^ A clinical study has revealed that PCSK9 inhibition may confer benefits during ACS through LDL-dependent mechanism.^[11]^ Intriguingly, beyond its effects on LDL metabolism, preliminary results suggest PCSK9 as a positive modulator of platelet activation in in vitro and in vivo models.^[15,30,31]^ On the basis of prior preclinical observations, we will demonstrate possible relationship between circulating PCSK9 and platelet reactivity using multiple platelet function assays in a Chinses ACS cohort. To the best of our knowledge, 1 study including Austrian ACS patients reported an association between increased serum PCSK9 levels and platelet aggregation in response to a single agonist ADP.^[27]^ It should be noted that a single measurement of platelet reactivity may lead to inaccurate evaluation of the in vivo status of circulating platelets.^[32]^ Here in our study, more detailed analysis of platelet reactivity will be undertaken by quantification of platelet activation markers and aggregation induced by various agonists.

In order to minimize confounding effects on platelet reactivity, several strengths in the methodology should be noted. For 1, to exclude any influence of antiplatelet drug effects on platelet status, only patients receiving dual antiplatelet therapy with aspirin and clopidogrel will be recruited. More specifically, blooding sampling will be taken immediately after the loading dose of aspirin (300 mg) and clopidogrel (300 mg) and before coronary angiography or percutaneous coronary intervention (PCI), because catheter procedure itself is traumatic to platelets and testing within 96 hours post-PCI seems highly unpredictable regarding ex vivo platelet reactivity.^[32,33]^ Further, experimental data revealed remarkable increase in PCSK levels at 12 to 96 hours after cardiac ischemia.^[34,35]^ In this regard, the optimal timing for testing platelet reactivity, along with its association with PCSK concentration should be prior to PCI procedures.

Preclinical studies have demonstrated that PCSK9 directly enhances platelet activation and in vivo thrombosis.^[36,30]^ Accordingly, Cammisotto et al^[37]^ found reduced platelet activation in patients with familial hypercholesterolemia after PCSK9 inhibitors administration, which was mechanistically linked to modulation of ox-LDL pathways. Indeed, during the inflammatory and oxidative processes of plaque rupture, the prothrombotic ox-LDL is generated from the modification of LDL by phospholipid oxidation.^[38]^ These observations prompt the hypothesis that PCSK9 may potentiate platelet reactivity via regulating ox-LDL-platelet interplay in the setting of ACS. Results from in vivo models revealed that ox-LDL, as a high-affinity ligand for platelet SR (e.g. LOX-1, CD36), facilitates platelet activation via binding to platelet surface.^[39]^ Interestingly, PCSK9 increased the expression of LOX-1 and ox-LDL uptake in macrophages in an inflammatory milieu.^[18]^ Whether PCSK9 is involved in the regulation of ox-LDL-platelet binding has never been evaluated in clinical settings. To this end, the association of serum PCSK9 and platelet-ox-LDL binding, an important mechanism for platelet-ox-LDL interplay, will also be explored in ACS patients.

Several limitations should be considered in this study. As this is by far the first analysis addressing the association of circulating PCSK9 with platelet reactivity and with platelet-ox-LDL binding in ACS Chinese cohort, we aim to recruit patients from a single center to achieve preliminary results. Given the limited sample size the intrinsic shortcomings of the cross-sectional design, future large prospective studies are warranted to confirm our findings. We notice that there are mounting evidence showing the direct effect of PCSK9 on platelet function in experimental conditions.^[18,30]^ In order to translate the observations into clinical settings, we emphasize to investigate the serum PCSK9 and its correlation with platelet reactivity using multiple assays, with additional goal to provide mechanistic insight from the perspective of platelet-ox-LDL interplay. If positive results are achieved, future studies are needed to unravel pathways downstream of ox-LDL-platelet binding to underlie the mechanism of PCSK9-mediated platelet activation.

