### 2.2. Study population and recruitment procedures

Patients aged 30 to 75 years presenting with ACS (unstable angina, ST-elevation or non-ST-elevation myocardial infarction) will be screened for eligibility. Voluntary patients will be enrolled after written informed consent is obtained. Immediately after the administration of loading dose of aspirin (300 mg) and clopidogrel (300 mg), blood sample will be harvested for further analysis of serum PCSK9, platelet reactivity and ox-LDL-platelet binding. To be more specifically, blood sampling will be performed before catheter procedures. Patients will be excluded with coronary stenosis < 50% as ascertained by coronary angiography. The inclusion and exclusion criteria are given in Table 1. The flowchart of the study is shown in Figure 1.

**Table 1 T1:** Inclusion and exclusion criteria.

Inclusion	Exclusion
• Patients aged 35–75 yr	• coronary stenosis < 50% as ascertained by angiography
• Presenting with ACS, including unstable angina, ST-elevation and non-ST-elevation myocardial infarction	• uncontrolled blood pressure, heart failure pulmonary dysfunction
	• severe hepatic, renal, hematologic, mental disorders, terminal illness (carcinoma, etc)
	• pregnancy or breastfeeding
	• reluctance to sign an informed consent form

ACS = acute coronary syndrome.

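### Lipid-lowering treatment, including PCSK9 inhibitors, is neither an exclusion nor adjusted for in the PCSK9 correlations, so it can bias them by an amount and in a direction the protocol does not let one know

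*Protocol article*

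**What the plan says.** **Claim about confounding.** The Discussion (section 3) states: "In order to minimize confounding effects on platelet reactivity, several strengths in the methodology should be noted". It then gives three measures: every patient receives the same two antiplatelet drugs, blood is drawn before angiography or PCI, and this also precedes the later rise of PCSK9 after ischaemia. Lipid-lowering treatment is not among them, nor is it among the limitations at the end of the Discussion.

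**Eligibility.** Table 1 (section 2.2) lists exclusions for insignificant stenosis, certain illnesses, pregnancy or breastfeeding, and refusal of consent. None concerns a lipid-lowering drug or a PCSK9 inhibitor.

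**Analysis.** Section 2.2.5 states: "The association of PCSK9 levels with platelet reactivity and ox-LDL-platelet binding will be evaluated by Spearman rank test". No adjustment or stratification is given. The one multivariable analysis is a logistic regression for on-treatment platelet reactivity. The Abstract ties that outcome to ADP-induced aggregation, and section 3.2.3 defines high on-treatment reactivity as MPAR_ADP above 59%.

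**What the article says about these drugs.** The Discussion describes patients after an ACS as staying at high risk "despite the current evidence-based treatments, including dual antiplatelet therapy and lipid-lowering agents". It cites a study that "found reduced platelet activation in patients with familial hypercholesterolemia after PCSK9 inhibitors administration, which was mechanistically linked to modulation of ox-LDL pathways". The Introduction says that PCSK9 raises circulating LDL and ox-LDL, and that both native and oxidised LDL affect platelets substantially.

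**The concern.** Serum PCSK9 is the only exposure. Platelet activation, aggregation and ox-LDL binding are the outcomes. By the article's own account, PCSK9 inhibitors target the exposure and also change platelet activation through the very pathway under study. Other lipid-lowering drugs act on LDL, which the article also links to platelet reactivity.

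If treated and untreated patients differ in measured PCSK9 and also in platelet function, a pooled rank correlation mixes two things: the association within each treatment group and the difference between the groups. The Spearman test as stated cannot separate them.

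The Conclusions intend to read positive results as reinforcing PCSK9-mediated modulation of platelet activation. That reading, and equally a null result, is hard to defend while treatment status is left in the correlation. The gap lies between the claim to minimise confounding and a design that leaves open the background treatment closest to the exposure.

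**Working it through.** **Inputs from the article.** Section 1.2.5: "a total of 115 patients will be recruited in the present study", after allowing for 20% attrition. Section 2.2.5: "All tests will be 2-sided with an alpha level of 0.05". Evaluable patients: 115 × (1 − 0.20) = 92, and the reverse step 92 / 0.80 = 115 is exact. No target correlation or power is stated, so 115 itself cannot be derived from the article. The bias does not depend on it.

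**Assumptions, not in the article.** Within each treatment group the Pearson correlation between PCSK9 and the outcome is 0.30. A share f of patients takes a drug that shifts measured PCSK9 by dx SD and the outcome by dy SD. The values of f, dx and dy are illustrative.

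**Formula for the pooled correlation (Pearson scale).**

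r = [0.30 + f(1−f)·dx·dy] / √{[1 + f(1−f)dx²]·[1 + f(1−f)dy²]}

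Example, f = 0.4, dx = +0.8, dy = −0.4:
- f(1−f) = 0.24.
- Numerator: 0.30 − 0.24 × 0.32 = 0.2232.
- Denominator: √(1.1536 × 1.0384) = 1.0945.
- r = 0.204. Simulation gives a Spearman of 0.192, in line with this.

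**Formula for power at n = 92.** The standard error on the Fisher z scale is √(1.06/89) = 0.109. Power = Φ(atanh(ρ)/0.109 − 1.96). With no drug effect: atanh(0.289) = 0.297; 0.297/0.109 − 1.96 = 0.77; power 78%.

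**Results** (simulated Spearman, 600,000 draws per row; power from the formula):

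| Share treated | Shift in PCSK9 | Shift in outcome | Pooled Spearman | Power |
|---|---|---|---|---|
| none | – | – | 0.289 | 78% |
| 30% | +0.5 SD | −0.3 SD | 0.246 | 63% |
| 40% | +0.8 SD | −0.4 SD | 0.192 | 43% |
| 5% (inhibitor only) | +3 SD | −0.5 SD | 0.227 | 56% |
| 5% (inhibitor only) | +3 SD | −1 SD | 0.187 | 41% |
| 40% | −0.5 SD | −0.4 SD | 0.319 | 86% |

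Opposite shifts weaken the correlation, and same-direction shifts inflate it.

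**What a reversal would take.** The numerator reaches zero when dx·dy = −0.30 / [f(1−f)]:
- f = 50%: −1.2 SD².
- f = 30%: −1.43 SD².
- f = 10%: −3.33 SD².
- f = 5%: −0.30 / 0.0475 = −6.3 SD².

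The 40% opposite-shift row has a product of 0.8 × (−0.4) = −0.32. A clear sign change appears only with shifts such as +2 and −1 SD in 50% of patients (pooled Spearman −0.16). With 10% treated, shifts up to +2 and −1 SD weaken the correlation (0.13 to 0.26) without reversing it.

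**What if there is no true association?** The moderate opposite shifts give −0.0768 / 1.0945 = −0.07, and the same-direction shifts give 0.048 / √(1.06 × 1.0384) = +0.05. At n = 92 these are significant in roughly 7 to 10% of trials, against 5% nominal. Shifts of a full SD on both sides in 30% of patients would raise this to 37 to 39%.

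**Does adjustment work?** A partial Spearman on treatment status, simulated at n = 92 with 1,500 trials per scenario over 10 to 50% treated and shifts up to +2 and −1 SD, kept power at 75 to 82%. The unadjusted figure without any drug effect was 79 to 81%. False positives stayed at about 2 to 3% per side.

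**The case against.** The strongest objection concerns the exposure side. Confounding needs an effect on measured serum PCSK9 as well as on platelets. The article nowhere says that a statin, another lipid-lowering drug or a PCSK9 inhibitor changes the measured concentration, or in which direction. Its evidence on inhibitors concerns platelets, and comes from familial hypercholesterolaemia. This stands. The shifts above are assumptions and even their sign is open. The article supports only that the drug class targets the exposure and alters the outcome.

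Second, the sentence on lipid-lowering agents describes patients after an event, not what they take at presentation, and nothing indicates that inhibitor use is common here. This also stands, so prevalence is unknown.

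Third, medication history and covariate lists commonly sit in a full protocol or analysis plan, which is not shown. A reader might infer that treatment will not be recorded, or that the logistic model will omit it. The article does not support that. But Table 1 is printed in full and the Spearman test is named as the main method. A covariate list for the logistic model would reach only ADP-based reactivity. P-selectin, GPIIb-IIIa, MPAR_AA and ox-LDL binding have no stated adjusted analysis.

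Fourth, the claim is to minimise confounding, not to remove it, and this is a pilot whose limitations mention sample size and the cross-sectional design. That limits the severity. It does not remove the case for a cheap repair.

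**Conclusion.** The point holds as a design improvement. Users of PCSK9 inhibitors are eligible, users of other lipid-lowering drugs are pooled with untreated patients, the main tests are unadjusted, and the article's own account gives reason to expect treatment to affect the outcomes.

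Under assumed moderate shifts the pooled Spearman moves from 0.29 to about 0.19 to 0.25, or to 0.32, depending on direction. The power figures illustrate the effect and are not a shortfall against a stated target, because the article states none.

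Two stronger readings are tempting and are not supported. One is that background treatment would reverse the association: none of the moderate scenarios changes sign, and a few inhibitor users alone would mainly weaken it. The other is that a significant result could be due to treatment status alone: with no true association the moderate shifts yield only about −0.07 or +0.05. Nor does the article establish that serum PCSK9 loses its meaning in a treated patient.

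**What to change.** 1. Add to the Table 1 exclusions any recent PCSK9-inhibitor exposure, with the look-back window defined in advance.
2. Record lipid-lowering treatment before sampling, including anything given between admission and the draw. The Abstract places the draw after the first maintenance dose, whereas section 2.2 and the Discussion place it immediately after the loading dose. These must be reconciled so that the period before sampling has one meaning.
3. Keep the Spearman tests and report each PCSK9 correlation also as a partial Spearman adjusted for that variable. Give the correlation in untreated patients as a sensitivity analysis. Adjust for treatment rather than for LDL level, since the article places LDL on the path from PCSK9 to platelets.
4. Name the same variable as a covariate in the logistic model.
5. Amend the Discussion so that the claim about confounding covers lipid-lowering treatment, or list it as a limitation.

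Cost: the loss of what may be a few PCSK9-inhibitor users, one medication-history field, and one degree of freedom per correlation. The sensitivity analysis in untreated patients will be less precise, in proportion to how many patients are treated.

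### Sampling before PCI does not fix the time since ischaemia, so the unadjusted PCSK9 correlations are liable to confounding or masking by onset-to-draw time and possibly ACS type

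*Protocol article*

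**What the plan says.** **Timing rationale.** The Discussion (section 3) lists features meant to limit confounding of platelet reactivity. Its main reason for sampling before catheterisation is that the procedure itself disturbs platelets. It then adds a second reason: "experimental data revealed remarkable increase in PCSK levels at 12 to 96 hours after cardiac ischemia". From this it concludes that "the optimal timing for testing platelet reactivity, along with its association with PCSK concentration should be prior to PCI procedures". The same section also says that circulating PCSK9 rises during ACS because of the ischaemia.

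**Sampling time.** Section 2.2 and the Discussion place the draw directly after the loading doses and ahead of catheterisation. The Abstract instead places it after the first maintenance dose, in the morning.

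**Population.** "Patients aged 30 to 75 years presenting with ACS (unstable angina, ST-elevation or non-ST-elevation myocardial infarction) will be screened for eligibility". Neither this section nor its Table 1 limits the time since symptom onset.

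**Analysis.** Section 2.2.5 states: "The association of PCSK9 levels with platelet reactivity and ox-LDL-platelet binding will be evaluated by Spearman rank test". No adjustment or stratification is attached to it. The one adjusted analysis is for a single outcome: "univariate and multivariate logistic regression will be used to analyze the association between PCSK9 levels with on-treatment platelet reactivity". No covariates are named for it.

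**The concern.** The rise that the article cites runs on a clock that starts at ischaemia. The sampling rule runs on clocks that start at drug administration and stop at the procedure. A patient who presents two hours after onset and one who presents two days after onset can both be sampled after loading and before PCI, yet stand at quite different points of the PCSK9 curve. The timing rule therefore leaves in place the source of PCSK9 variation that the article itself names.

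If time since onset, or the type of ACS, also moves the platelet measures, a Spearman coefficient mixes any PCSK9-platelet relation with the effect of when in the event the patient was sampled. The result could be a spurious correlation or a hidden real one. This matters because the Conclusions section would read positive results as support for modulation of platelet activation by PCSK9.

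**Working it through.** **1. Evaluable number.** Section 1.2.5 says "with the consideration of estimated attrition rate of 20%, a total of 115 patients will be recruited". Evaluable patients: 115 × (1 − 0.20) = 92, and back again 92 / 0.80 = 115. The article gives no effect size or power, only "According to previous research", so 115 cannot be rederived beyond this step.

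**2. What 92 patients can detect.** Section 2.2.5: "All tests will be 2-sided with an alpha level of 0.05". By Fisher's z, r = tanh[(1.960 + 0.842) / √(92 − 3)] = tanh(2.802 / 9.434) = tanh(0.297) = 0.289 at 80% power. With the usual variance factor of 1.06 for Spearman it is 0.297.

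**3. Set-up for the illustration.** Let T be onset-to-draw time, with correlation *a* with PCSK9 and *b* with platelet reactivity, and no PCSK9-platelet link given T. The induced Pearson correlation is *a* × *b*, and for normal variables the Spearman value is (6/π) × arcsin(*ab*/2). For *a* = *b* = 0.5: (6/π) × arcsin(0.125) = 0.239. **The article gives neither *a* nor *b*, so every value below is an assumption.**

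The unadjusted test uses t = ρ√[(n − 2)/(1 − ρ²)]. The partial coefficient is (ρ_xy − ρ_xT·ρ_yT) / √[(1 − ρ_xT²)(1 − ρ_yT²)], tested on n − 3 degrees of freedom.

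**4. No true link, n = 92, 8,000 simulated studies per row.**

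| a (PCSK9) | b (platelets) | Mean Spearman | Unadjusted rejects | Partial rejects |
|---|---|---|---|---|
| 0 | 0 | 0.00 | 4.9% | 4.8% |
| 0.2 | 0.2 | 0.04 | 6.6% | 5.0% |
| 0.3 | 0.3 | 0.09 | 13.1% | 5.1% |
| 0.4 | 0.4 | 0.15 | 30.2% | 5.1% |
| 0.5 | 0.5 | 0.24 | 63.2% | 5.1% |
| 0.5 | 0 | 0.00 | 4.9% | 4.9% |
| 0.5 | −0.5 | −0.24 | 62.4% | 5.7% |

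The row *a* = 0.5, *b* = 0 is decisive for how the point may be worded: when time moves PCSK9 only, there is no inflation. At the other end, the spurious 0.24 is not far below the 0.289 that 92 patients detect with 80% power.

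**5. True partial correlation 0.3, n = 92: power.**

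| a | b | Unadjusted | Partial |
|---|---|---|---|
| 0 | 0 | 79% | 79% |
| 0.5 | 0 | 67% | 78% |
| 0.3 | −0.3 | 38% | 77% |
| 0.5 | −0.5 | 5% | 74% |

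**6. Price of adjustment.** One term for time and two for three ACS types use 3 degrees of freedom. The detectable r becomes tanh(2.802 / √86) = tanh(0.302) = 0.293, against 0.289.

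**The case against.** The strongest reply is that confounding needs two arms and the article documents only one. It links ischaemia to PCSK9. It gives no time course for platelet reactivity and no difference in PCSK9 or platelet function between unstable angina, NSTEMI and STEMI. The Introduction reports more platelet-bound ox-LDL in ACS than in stable disease, but stable patients are not enrolled here. This stands. A reader might infer that the correlations are confounded, or that the false-positive rate is 63%. The document supports neither: the rate depends on assumed correlations and may be the nominal 5%.

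Other parts of the reply also carry weight:

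- If time acts on platelets only through PCSK9, which fits the study's hypothesis, time is not a confounder and adjusting discards useful variation in exposure. This is a reason to show both coefficients.
- The near-5% rejection after adjustment assumes that time is measured without error.
- A reader might infer that the whole plan is unadjusted. It is not: the multivariable logistic model covers on-treatment reactivity. It does not cover the activation markers or ox-LDL binding. The article also does not name Spearman as the primary analysis.
- A reader might infer that onset time will not be collected. The article does not say so, and a condensed article may leave the data fields and covariate list to a fuller document.
- Catheter trauma to platelets is a separate and sufficient reason to sample before PCI. The study is a pilot whose limitations already concede the weakness of a cross-sectional design.

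None of this rescues the inference itself. It is stated in the article, it does not follow from the evidence cited for it, and the analysis stated for most outcomes does nothing about the source of variation it names.

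**Conclusion.** The point holds as a liability, not as a demonstrated bias. Sampling before PCI, or directly after loading, does not place patients before, inside or after the 12 to 96 hour rise. With no onset window, pooled ACS types and unadjusted Spearman tests, the correlations of PCSK9 with platelet reactivity and with ox-LDL binding may be inflated or masked by onset-to-draw time. The case for ACS type is weaker and rests on plausibility.

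Size and direction are unknown. For assumed equal, same-sign correlations from 0 to 0.5 the false-positive rate runs from about 5% to 63%. If time affects PCSK9 only, it stays at 5% and the sole loss is power (79% to 67% for a true partial correlation of 0.3, with *a* = 0.5). The sample-size figure is unaffected. The change is worth making because it is cheap and onset time may be hard to recover reliably after enrolment.

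**What to change.** 1. Record the time from symptom onset to blood draw for every patient.
2. For all platelet and ox-LDL-binding measures, report a partial Spearman coefficient (or a rank or linear regression) adjusted for onset-to-draw time and ACS type, beside the unadjusted coefficient.
3. Include the same two covariates in the logistic model for on-treatment reactivity.
4. Add a sensitivity analysis restricted to draws less than 12 hours from onset. The boundary comes from the experimental data that the article cites, so it is a guide and not an established cut-off in these patients.
5. Remove from the Discussion the inference that sampling before PCI deals with the PCSK9 time course. The argument from catheter trauma can stay.
6. Reconcile the Abstract, which samples after the first maintenance dose, with section 2.2 and the Discussion, which sample directly after loading. The two imply different times from onset.

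**Cost.** One recorded time, some analysis wording and 2 to 3 degrees of freedom. Onset time is imprecise in unstable angina, so adjustment there will be incomplete, and confounding by severity can remain. The restricted analysis will have fewer than 92 patients, by a number that the article does not allow one to predict.
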